#### 2.4.6 Psychophysical assessment of photoreceptor mechanisms.

*Psychophysics testing with pupil relay system.* Psychophysical tests will be conducted using the Metropsis system (Cambridge Research Systems, Rochester, UK). Visual stimuli will be presented on a colour-calibrated three-primary 32-inch LCD with a 10-bit colour resolution and a refresh rate of 120 Hz. The field of view on the monitor was restricted to a circular blackout cutout approximately 38 cm in diameter that was placed in front of the monitor. The monitor was calibrated by the manufacturer at setup. While the photopic background ensures saturation of rods, the activation of melanopsin cannot be independently controlled. In all experiments, participants will view stimuli with their dominant eye through a pupil relay system: an artificial pupil restricts the pupil diameter to 1.5 mm. Image projection is done by relaying the image from the plane of the external pupil through an assembly of two lenses onto the plane of the participant’s pupil. With this setup, the image is flipped horizontally, which we account for in the experimental setup. We correct for the participant’s refractive error before starting the first experimental block. This is achieved by adjusting the distance between the two lenses, which shifts the focal plane to compensate for the refractive error of the human eye. By adjusting the focus, the image from the artificial pupil is brought into focus on the plane of the human pupil. This ensures a sharp image is formed without altering the magnification of the optical setup. This correction is maintained for all subsequent measurements. The experimenter controls the distance between the lenses. The participant is instructed to indicate when a change in distance causes the image to become blurred. The experimenter then adjusts the distance in the opposite direction until the participant indicates that the image is clear again. Participants’ responses will be recorded on a response box (Black Box Toolkit Ltd., England). Two tasks will be carried out with this setup, a 10-axis Cambridge Colour Test (CCT) for screening purposes, and a temporal contrast sensitivity task (tCS task) for the perceptual threshold as main outcome, described in the following. Before the tasks, participants adapt to a neutral grey background at $60\;{cd/m}^{2}$ for one minute.

*Silent substitution of post-receptoral mechanisms.* We will probe the sensitivity for luminance and of the colour-opponent processes by means of (1) joint modulation of all three cones to target the luminance channel (L+M+S*), (2) isolated modulation of S-cones keeping the luminance channel constant (S*), and (3) antagonistic modulation of L- and M-cones to target the red-green channel (L–M*). The asterisk in condition labels indicates the lack of control over melanopic stimulation with the RGB monitor compared to the 6-LED stimulation device employed during pupillometry, e.g. S* is the S-cone isolating condition on the RGB monitor, where melanopsin activation cannot be kept at a constant level, while S is the S-cone isolating condition fixing L-, M-, and melanopsin-activation while modulating S activity. Maximum contrasts are predefined by the given colour gamut of the monitor (L+M+S*: 100%, S*: 51%, and L–M*: 6%) and starting values are partly lower as a trade-off between experiment length and visibility of the stimuli (L+M+S*: 90%, S*: 35%, and L–M*: 6%). The accidental activation of melanopsin will not be monitored. Effects of ipRGCs on the psychophysical tasks performance are assumed to be minimal.

*Post-receptoral temporal contrast sensitivity.* In the two-alternative forced choice (2AFC) tasks, stimulus contrast varies according to a staircase method, approaching the participant’s contrast threshold in relative steps. Contrast sensitivity is calculated from the threshold values. Within one test of the tCS task, different temporal frequencies, 2 and 8 Hz, are presented in interleaved order for one condition or photoreceptor mechanism. Participants determine whether the stimulus appears right or left from the centre of the screen with a left or right button press. Location varies randomly. After completion of three conditions, we will reiterate over the conditions twice, yielding nine tests per block. During the light exposure session (Sect 2.4.2), the participant will learn the task procedure, completing all 9 tests to achieve comparable light exposure levels. Tests are expected to last longer due to unfamiliarity in the light exposure session.

#### 2.4.7 Circadian phase measurements

Circadian phase will be determined by body temperature, salivary melatonin concentration, and DLMO.

*Telemetric core body temperature.* Temperature in the gastrointestinal tract will be measured through a telemetric pill. Data will be sent from ingestible pills from the e-Celsius^®^ Performance System 261 (BodyCap, Hérouville Saint-Clair, France) with a sampling rate of 2 Hz, providing measurements every 30 seconds. Device connects to an external device when in proximity and sends data via RFID. The first pill will be administered in the beginning of each session (light exposure session, dim light session, forced-desynchrony session) and another one 20 hours into the forced-desynchrony protocol, as the first pill will be excreted in the stool after 24–48 hours. The device is CE-certified. As the device is not MRI safe, participants will receive a wristband indicating that they cannot enter an MRI scanner. Temperature data will be used to estimate the person-specific circadian period τ with available data dim light session, the subsequent adaptation night and the forced-desynchrony session as described in Sect 2.6.1.

*Salivary hormone concentrations.* Melatonin and cortisol concentration will be obtained using from saliva samples that are sampled approximately every 45 minutes throughout the forced-desynchrony, except during sleep periods. Saliva will be sampled approximately every 30 minutes starting 4 hours prior to bedtime until habitual bedtime. Salivette^®^ collection devices were chosen for saliva samples and bioassaying for the extraction of hormone concentration saliva collection. In brief, participants chew on a cotton swab for 5 minutes and place it into a plastic collection tube. The Salivette^®^ will then be centrifuged for 3 minutes at 3,000 rpm and frozen at -20^∘^ for temporary storage. Biological samples will be collected initially in the laboratory and then sent to external laboratory companies for further processing. Saliva samples of at least 0.5 mL will be taken from the participants using Salivettes (Sarstedt, Nürnberg, Germany). Melatonin and cortisol will be determined by ELISA (CRTN-96, NovoLytiX GmbH, Switzerland, as commissioned work. The analyses have the typical specifications: limit of quantification 0.3 – 30 ng/mL, detection limit ≤0.3% ng/mL, intra-assay precision ≤6%, and mean inter-assay precision ≤10%. All samples will be destroyed after completion of the hormone analyses. The salivary melatonin concentration during forced-desynchrony is used to identify the participant-specific circadian period. Dim light melatonin onset (DLMO) will be determined for both evenings, using the hockey stick algorithm [52].

#### 2.4.8 Homeostatic processes.

We will collect data from multiple modalities to accurately assess the homeostatic state.

*Subjective sleepiness.* As measure of subjective fatigue, participants will be asked to report their sleepiness via the Karolinska Sleepiness Scale (KSS) at every measurement block.

*Distal-proximal temperature gradient.* Wireless iButton devices will be used to monitor skin body temperature at two pre-defined locations on the skin, one proximal, e.g. near the neck, and one distal, e.g. on one ankle. The thermometry devices will also be attached to the skin. From the sensor readings, the temperature gradient between the distal and proximal skin (DPG) will be calculated, as it has been shown to vary with sleep propensity [53]. Sampling frequency for skin temperature is 2 Hz. Information derived from skin temperature may feed into exploratory analyses, statistically separating effects of the circadian rhythm and homeostatic processes or the sleep-wake rhythm.

*Cardiovascular and respiratory monitoring.* For blood pressure monitoring during the experimental sessions, we will employ the ABPMpro device (SOMNOmedics AG, Randersacker, Germany). Blood pressure measurements will be taken twice per measurement block. The ABPMpro can be extended by a 3 EGC sensor (Holter). We will attach the surface electrodes to the participant’s chest and ribs for impedance cardiography throughout the 40 hours forced-desynchrony. We may derive outcomes such as heart rate, heart rate variability, and breathing frequency from measurements, to evaluate activity of the autonomous nervous system in exploratory analyses.

*Alertness and Vigilance.* In every block, participants will complete a 10-minute visual psychomotor vigilance test. The test will be delivered on the PVT-192 Psychomotor Vigilance Task Monitor (Ambulatory Monitoring, Inc., Ardsley, USA; [54]) and serves as a measure of alertness, vigilance or conversely, sleepiness. As part of the test, participants are tracking a visual stimulus, a digit counter that appears at random on the device display and starts counting up in milliseconds. The display acts as both, the stimulus and the performance feedback display. Participants have to respond as fast as possible to the stimulus with a button press using the thumb of their dominant hand. Time between stimulus presentation and response constitutes the participant’s response time if they are below or equal 500 ms. Median reaction time, lapse probability (reaction time > 500 ms) per session, and mean of fastest 10% reaction times are used as main outcome measures of alertness.

#### 2.4.9 Ocular structure and function.

All measurements of ocular physiology will be performed on the left and the right eye. Data on various aspects starting from light incidence at the retina to structure of the retinal layers will be collected. All applied procedures are standard procedures that are routinely carried out during a visit to the ophthalmologist. The ophthalmologist of the team will review concerning results and write a physician’s letter in case of incidental findings.

*Photography of fundus and anterior segment.* During the first session, coloured images of the anterior segment (including iris) and the fundus will be made.

*Optical toherence tomography measurements.* We will repeatedly capture structural images of the retina and the cornea (without concomitant fundus photography due to light exposure), to obtain estimates of corneal and macular thickness using time-domain optical coherence tomography system (OCT-2000, Topcon Corporation, Tokyo, Japan).

*Intra-ocular pressure.* For measurements of intra-ocular pressure (IOP), we will use a Non-Contact Tonometry (NT-2000 NC Tonometry, NIDEK CO., LTD., Japan). The outcome variable for one measurement block is the arithmetic mean of three estimates, quantified in millimetre of mercury. Non-contact tonometry involves administration of an air-puff to the eyes, which may lead to a temporary sensation of dryness or discomfort in the eyes.

#### 2.4.10 Subjective well-being.

Participants stay under laboratory conditions for several days. This touches upon most aspects of everyday like, for example, eating habits during this period will be monitored. However, participants are allowed to have a minimum of 30 minutes of their own time during each awake period. Additionally, their emotional state is closely tracked with mood questionnaire (I-PANAS-SF) [55].

*Enrichment.* During the experimental sessions, participants will not be able to use their phones, or any other device indicating time of day, nor will they be allowed to receive visitors. Relatives or close ones may be given a phone number to call the study team on-site in the event of an emergency. For enrichment during their stay, they may bring their own media or reading material, or may choose from pre-selected music, podcasts, or audiobooks.

*Physical needs.* During the laboratory visits, participants will have access to water ad libitum to maintain hydration. For their nutritional needs, they will be provided with shakes containing a balanced composition of macronutrients (carbohydrates, protein, fats, and fibre) and essential micronutrients. Shake intake will be scheduled exclusively during wakefulness, and participants will be instructed to consume the shakes at a frequency consistent with their usual number of main meals per day (typically between two and four meal times). To accurately determine caloric intake during the 40-hour forced-desynchrony session, each participant’s base metabolic rate (BMR) will be calculated using the Mifflin-St. Jeor equation, which accounts for sex, body weight, and height [56]. The BMR will then be adjusted for a sedentary lifestyle using a correction factor of 1.2, irrespective of participants’ habitual levels of physical activity.

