### 1.3 Ultra-short sleep-wake forced-desynchrony protocol

Here, we will employ a 40-hour forced-desynchrony (FD), multiple-naps protocol with a night-day/light-dark (LD) cycle totalling 3h45m. In this protocol, sleep pressure is kept at a constant low level by rapidly alternating between sleep and wake periods (i.e. regular naps). Other homeostatic influences like food intake and activity will be adapted to the ultra-short rhythm. External influences including ambient temperature and dim light during wakefulness are kept constant to minimize the influence on the circadian rhythm.

In the literature, a similar protocol has been successfully implemented before, scheduling sleep and wake time in a 2:1 ratio of imposed day length of 3h45m [26,27]. 150 min (2h30m) wake intervals in dim light (< 10 lux) provide opportunity for measurements and are followed by 75 min (1h15m) sleep intervals in darkness. The protocol lasts 40 hours, yielding 11 repeating light-dark (LD) cycles or measurement blocks.

This study will isolate circadian effects on early stages of visual processing from homeostatic effects with a short forced-desynchrony protocol. Participants will stay in the laboratory for 40 hours, which will cover, on average, 1.5 circadian periods.

They will adhere to an ultra-short sleep-wake rhythm schedule, comprised of 2h30m (150 minutes) of wake time and 1h15m (75 minutes) of sleep opportunity. During each scheduled instance of wakefulness, a series of (psycho-)physical parameters will be measured in order to determine sensitivity of photoreceptor mechanisms, circadian phase, sleep pressure, and other possible physiological outcomes assumed to undergo circadian change. Specifically, we will repeatedly collect data on: (1) psychophysical performance, and more specifically temporal contrast sensitivity (tCS) (2) the immediate maximum pupil constriction amplitude (pupillary light response, PLR) to carefully crafted light stimuli, (3) intra-ocular pressure, (4) structural properties of the cornea and retina (5) salivary melatonin concentration, (6) mood, and (7) sleepiness; additionally, there will be continuous measurements of physiological functions (8) temperature in the core body and the proximal-distal gradient of skin temperature, (9) heart rate variability via electrocardiography (ECG), and (10) interstitial glucose concentration.

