The second laboratory visit starts with one evening session under dim-light conditions and another adaptation night when participants will have a full night of sleep (8 hours), followed by the forced-desynchrony session that involves 40 hours on a ultra-short sleep-wake cycles. Participants will enter the lab five hours before their habitual bedtime and complete a four-hour dim light session. The forced-desynchrony session starts 60 minutes after the end of the adaptation night. During the first 60 minutes, people have opportunity for personal hygiene and will be equipped with the sensors. 40 hours will be spent in constant environmental conditions, with a temperature of 20^∘^C, and no time cues are provided. The main room is lit with dim light at < 10 lux, so that light exposure is constant except during light exposure due to visual tests and during sleep. For an overview of the study period, see Fig 1.

The first ultra-short sleep-wake will start with a wake period. During wake time, all other tests will be carried out while sitting. To reach the devices, participants have to walk up within the laboratory for up to 30 meters. During wake time, light isocaloric snacks and water that are heated up to body temperature will be provided at three opportunities, mirroring breakfast, lunch, and dinner. After experiments, a remaining wake time of 30 minutes can be spent freely. The 2h30m wake period is followed by a 1h15m sleep period, that will be spent in a recumbent position. Participants will put on a light-tight sleep mask.

An overview timeline during the forced-desynchrony session is shown in Fig 2, and a more detailed timeline of single measurement blocks in Fig 3.

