**Fig 3 pone.0300405.g003:**
[figure not shown]
Detailed timeline of a single measurement block during the 40-hour forced-desynchrony protocol. This figure outlines the sequence and duration of measurements (grey background) and activities (white background) within one 2h30m wake period, including psychophysical tests, pupillometry, physiological measurements, and scheduled meal times. The continuous measurements, core body temperature (CBT), continuous glucose monitoring (CGM), and electrocardiography (ECG), are indicated at the bottom.

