*Metabolic activity.* We will monitor metabolic activity starting the morning after the light exposure session for a total of 14 days, thereby extending into the stabilisation period after the forced-desynchrony session. A continuous glucose monitoring (CGM) system (FreeStyle Libre 3, Abbott Laboratories, Alameda, California) is used to monitor participants’ glucose profile. The small sensor is placed on the skin of the back of the upper arm, and measures the glucose concentration in the interstitial fluid (ISF). As blood glucose levels seem to rise in food anticipation and reflect meal-time history of multiple days, they will likely not be in line with the meal-timing imposed during the ultra-short sleep/wake rhythm [44]. Participants will not have access to their glucose readings during wear time, as feedback may interfere with natural eating patterns. Glucose levels are quantified in mg/dL.

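### The two descriptions of feeding in the forced-desynchrony session conflict, neither gives a time unit, and the natural reading of one departs from the ultra-short cycle and permits a 24-hour fed/fasted pattern.

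*Protocol article*

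**What the plan says.** Section 1.3 sets a principle for the session: "Other homeostatic influences like food intake and activity will be adapted to the ultra-short rhythm".

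Two later sections describe the feeding itself:

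- **Section 2.3**, in its account of the ultra-short cycle: "light isocaloric snacks and water that are heated up to body temperature will be provided at three opportunities, mirroring breakfast, lunch, and dinner". It does not say whether three means per wake period, per 24 h or per session.
- **Section 2.4.10**, under physical needs, for the laboratory visits: "participants will be instructed to consume the shakes at a frequency consistent with their usual number of main meals per day", with the range "typically between two and four meal times". The only timing rule is "Shake intake will be scheduled exclusively during wakefulness". The energy calculation that follows is for the 40-hour session.

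Two other places bear on timing. The caption of Fig 3 lists what happens "within one 2h30m wake period, including psychophysical tests, pupillometry, physiological measurements, and scheduled meal times". Section 2.4.3 says of glucose levels that "they will likely not be in line with the meal-timing imposed during the ultra-short sleep/wake rhythm". Section 2.3 also says that participants receive no time cues. No section fixes clock times for meals or an overnight fast.

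**The concern.** The design works only if behavioural influences repeat with each 3h45m cycle, so that what varies over about 24 h can be credited to the clock. Feeding is one of the influences that Section 1.3 names. If intake follows a habitual daily count instead, some measurement blocks are fed and others fasted, in a pattern that differs between participants.

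Eq. (4) has an intercept, a sine term, a cosine term and participant effects. It has no feeding term. Section 2.6.1 searches for the period between 20 and 28 h, so a 24-hour feeding pattern would lie inside that range. Participants come from a stabilisation period with fixed sleep times and approximate meal times, and every session starts 60 minutes after the adaptation night ends. A pattern tied to habitual mealtimes would therefore tend to be aligned across participants rather than average out. A rhythm in pupil response or contrast sensitivity (H1a–H1d, H2a–H2c) could then reflect meals as well as the clock.

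**Working it through.** **Inputs from the article.** Wake 2.5 h and sleep 1.25 h (Section 1.3); 40 h and 11 blocks (Section 1.3); two to four meals (Section 2.4.10); three opportunities (Section 2.3); period range 20 to 28 h (Section 2.6.1).

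**Schedule.** Cycle = 2.5 + 1.25 = 3.75 h. Cycles per 24 h = 24/3.75 = 6.4, which reproduces the figure in Section 2.2. Ten full cycles plus one wake period = 37.5 + 2.5 = 40 h, so 11 blocks fit.

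**Intakes under each reading.**

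| Text | Unit assumed | Intakes in 40 h |
|---|---|---|
| Section 2.4.10 | per 24 h | 2, 3, 4 × 40/24 = 3.3, 5.0, 6.7 |
| Section 2.4.10 | per wake period | 2, 3, 4 × 11 = 22, 33, 44 |
| Section 2.3 | per session | 3 |
| Section 2.3 | per 24 h | 3 × 40/24 = 5 |
| Section 2.3 | per wake period | 3 × 11 = 33 |

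The readings span 3 to 44 intakes. On the per-24-h reading of Section 2.4.10, the average number of blocks without a meal is at least 11 − 3.3 = 7.7, 11 − 5 = 6 and 11 − 6.7 = 4.3 for two, three and four meals.

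**Could eq. (4) separate a 24-hour feeding pattern from the clock?** Forty hours hold 40/24 = 1.67 cycles. Even at the ends of the searched range, the two rhythms drift apart by only 40 × (1/20 − 1/24) = 0.33 of a cycle, or 40 × (1/24 − 1/28) = 0.24 of a cycle. With 11 points per participant and no feeding term, the answer is no.

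**How large could the 24-hour component be?** The article gives no meal times, so these are assumptions. Block 1 starts at 08:00, and the meal pattern also held on the day before. Hours since the last meal, y, were regressed on the clock as y = c0 + c1·sin(2πt/24) + c2·cos(2πt/24), at t = 3.75(i − 1) for block start and 1.25 h later for mid-wake, i = 1 to 11. Even spacing means meals every 12, 8 or 6 h from the start of block 1.

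| Meals per 24 h | Assumed habitual times | R² mid-wake | R² block start | Amplitude mid-wake | Even spacing: R² mid-wake | Even spacing: R² block start |
|---|---|---|---|---|---|---|
| 2 | 08, 19 h | 0.17 | 0.00 | 2.2 h | 0.01 | 0.10 |
| 3 | 08, 13, 19 h | 0.52 | 0.32 | 4.1 h | 0.02 | 0.09 |
| 4 | 08, 12, 16, 20 h | 0.49 | 0.25 | 3.5 h | 0.03 | 0.06 |

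Moving a meal that falls in a sleep period to the next wake period changes no R² by more than 0.05. With these habitual times a session that begins with a meal contains 4, 6 or 8 meals, slightly above the averages, and 7, 5 or 3 blocks have none. With the same intake at the same point of every wake period, hours since the last meal is constant after block 1, and this component vanishes.

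**The case against.** The strongest reply is that the text does not state a daily feeding rhythm. A reader might infer that the protocol builds in a 24-hour feeding cycle and a time cue. The documents do not support that: Section 2.4.10 fixes a number of meals, not clock times, and under even spacing the same number gives almost no 24-hour component at mid-wake. A reader might also count three competing schedules, but Section 1.3 is a principle, so there are two descriptions and a principle. Nor does a glucose objective fail, because Section 2.4.3 states an expectation about glucose and not an objective.

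The paragraph in Section 2.3 runs through one short cycle in order: wake period, food, free time, sleep. Three small intakes per wake period, imitating a normal day, is a fair reading. It agrees with Section 1.3, Section 2.4.3 and the Fig 3 caption, and on that reading the sequence repeats every 3h45m and gives no time-of-day cue. Fig 3 itself, which may show the schedule, is not available here, and exact meal times may be left to the full protocol.

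All of this stands against the stronger reading. It does not remove the conflict. A participant's usual number of meals per day describes life at home, where a day is 24 h. Reading it per short day means 22 to 44 shakes in 40 h. Even then, a fixed three and an individual two to four disagree, as do snacks and shakes. This is not detail lost in condensing: the article states the rule twice, differently, and the natural reading of one version goes against its own principle.

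**Conclusion.** The point holds as an inconsistency with a possible consequence for the primary inference. Sections 2.3 and 2.4.10 conflict on food and count and omit the time unit. On its natural reading, Section 2.4.10 gives about 3 to 7 meals over 11 blocks, which contradicts Section 1.3 and fits poorly with Section 2.4.3 and the Fig 3 caption.

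The confounding with eq. (4) is conditional. It requires both the per-24-h reading and meals placed at habitual times of day. Under assumed times of that kind, a 24-hour cosine explains 17% to 52% of the variation in hours since the last meal at mid-wake, and 0% to 32% at block start. Under even spacing the figures are about 1% to 3% and 6% to 10%. These describe fed/fasted state only. The documents give no figure for how strongly feeding affects pupil response or contrast sensitivity, so no bias in the Bayes factor can be stated.

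**What to change.** Reconcile Sections 2.3 and 2.4.10 with the principle in Section 1.3. State one rule for the forced-desynchrony session, with its time unit, under which intake is tied to the 3h45m cycle and recurs in the same way in every wake period. Make clear that the habitual meal count and the breakfast, lunch and dinner comparison do not set a 24-hour schedule. Say whether snacks or shakes are meant, and check that Fig 3 agrees. Keep the total energy calculation of Section 2.4.10. Record the time and amount of each intake, so that any departure can be examined in the exploratory analyses.

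The number and size of portions are for the investigators to set. The cost is revised wording, portion preparation, and smaller, more frequent intakes for participants than a habitual daily count would give.
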